### Statistical analysis and power calculation

Statistical power calculations were based on the methodology for stepped-wedge randomised trials outlined in Hussey and Hughes [33]. These were calculated specifically for the primary outcome ‘alcohol-related hospital admission rates (narrow)’ obtained from the Local Alcohol Profiles for England (LAPE)^4^ extracted for all 10 GM local authorities. Statistical power analyses were conducted at local authority level rather than at the level of the intervention area (the equivalent of one to three LSOAs) because the exact areas and comparisons had not been determined, but this aggregated level provided indications within the stepped wedge context. The mean standardised alcohol-related hospital admission rate in these local authorities for the year 2014 was 207 (per 100,000 people) with a maximum temporal standard deviation per site of 17.2 (range within sites 5–17) and a coefficient of variation across sites of 4.35. With 10 areas and 12 month follow-up (i.e. when all areas have received the intervention and a minimum of 1-month post-intervention follow-up), and a statistical significance level of 5% and statistical power of 90%, the proposed study will be able to detect a 10% average difference in rates compared to baseline. For an intervention to be effective and cost-effective a minimal reduction in key indicators of 10% seems reasonable. Statistical analyses will use standard mixed-effects models with an indicator of when the intervention was introduced in each area and a time component to account for the repeated measures nature of the data.

With respect to the comparison with propensity matched controls and synthetic controls in which time trends will be compared within the larger area of between different areas, no additional clustering occurs. Assuming a standard comparison of independent means, 1-sided test, and significance level of 5%, changes in alcohol-related hospital admission rate in the intervention LSOA, relative to the selected comparison area, yield an 84% statistical power to detect a similar 10% decrease. Trends in matched areas are evaluated using mixed-effects log-rate models as previously used at lower-tier local authority area level for alcohol-related hospital admissions [9] and alcohol-related crime rates [10] in England.

To create the synthetic controls Bayesian structural time series methods will be used [37, 38]. These ‘synthetic areas’ will be based on weighted averages of other GM local areas, where the weights are chosen so the synthetic GM area most closely resembles the actual GM area before the intervention started [39]. Trends between the measured and the modelled, counterfactual, outcomes in the synthetic controls (generated using Bayesian structural time series) will be interpreted as the intervention effect.

In these statistical power calculations we have not taken into account any potential ‘spill-over’ effects, such as described for a community action programme in Sweden [40], and which implies that the above may be an underestimation of the true statistical power (or, conversely, of the minimal detectable effect). It is unclear how these should be modelled, and therefore, as outlined above, no LSOAs immediately adjacent will be matched.

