### Setting

All Greater Manchester (GM) boroughs within the study setting have higher than England averages for alcohol-related mortality, ranging from 46.7 in Trafford to 71.9 per 100,000 in Manchester [32]. GM is heterogeneous in terms of its application of licensing policy: in a recent national study, only one local authority was classified as having high licensing policy intensity (two local authorities were medium, five low and two passive in terms making use of cumulative impact areas and/or declining licences [9]).

CICA will be rolled out sequentially across specifically targeted areas in all 10 local authorities, with the sequence randomly assigned by the research team, so that it will eventually (within the timespan of a year) be delivered in all areas. The intervention areas themselves within each local authority will be formed around pre-existing communities in LSOA locations. For data analysis purposes, the chosen LSOAs that represent each community combine to make the ‘intervention area’ unit of analysis. For example, the smallest intervention area encompasses one LSOA (mid-year population estimate of 1648) and the largest contains three LSOAs (mid-year population estimate combined of 5586).

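### The between-site coefficient of variation of 4.35 in the stepped-wedge power calculation cannot be right as printed, and the printed inputs do not give the stated 90% power for a 10% difference under the most natural layout

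*Protocol article*

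**What the plan says.** All the inputs are in the Protocol article, mostly under Statistical analysis and power calculation.

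- Method: "Statistical power calculations were based on the methodology for stepped-wedge randomised trials outlined in Hussey and Hughes [33"].
- Mean rate of narrow alcohol-related admissions in the 10 Greater Manchester local authorities: "for the year 2014 was 207 (per 100,000 people").
- Variability: "with a maximum temporal standard deviation per site of 17.2 (range within sites 5–17) and a coefficient of variation across sites of 4.35". Neither a percent sign nor a rate unit follows the 4.35.
- Design: "With 10 areas and 12 month follow-up (i.e. when all areas have received the intervention and a minimum of 1-month post-intervention follow-up").
- Result, stated relative to the baseline rate: "statistical significance level of 5% and statistical power of 90%, the proposed study will be able to detect a 10% average difference in rates".

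The Setting section adds that roll-out is sequential, "with the sequence randomly assigned by the research team, so that it will eventually (within the timespan of a year) be delivered in all areas". For this calculation the article does not give the number of areas crossing at each step, the period length, whether the test is one- or two-sided, or the reference distribution.

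**The concern.** In the Hussey and Hughes model the between-site variance is one of two variance inputs. A reader who takes 4.35 at face value as a coefficient of variation gets a between-site SD of 4.35 × 207 ≈ 900 per 100,000 around a mean of 207, which ten admission rates cannot have. The number sits inside the power statement for the randomised comparison, not in background text.

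A second problem appears when the formula is run. The layout the text most naturally describes returns neither 90% power nor a 10% detectable difference. What is at stake is whether the power statement can be checked and reused: a reader cannot tell which between-site variance was entered, or what layout and test produced the 90%.

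**Working it through.** **Inputs.** Printed: I = 10 areas; mean 207; within-site SD σ = 17.2 (σ² = 295.84); significance level 5%; difference 10% × 207 = 20.7. Assumed, because not printed: one area crossing per monthly step, T = 11 or 12 periods with the first all-control, two-sided z test, and σ applying to each area-period.

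**1. Upper bound on the coefficient of variation.** For n non-negative values with mean m, Σx² ≤ (Σx)² = n²m². The population variance is therefore at most nm² − m² = (n − 1)m², so the CV is at most √(n − 1) = √9 = 3.00. With the sample SD the bound is √n = √10 = 3.16. It is reached only when nine of the ten values are zero. A ratio of 4.35 exceeds both bounds.

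**2. Possible meanings of 4.35** (τ = between-site SD):
- ratio: τ = 4.35 × 207 = 900 (impossible)
- misplaced decimal, 0.435: τ = 90
- percentage, 4.35%: τ = 9.0
- an SD already in rate units: τ = 4.35

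**3. Attempt to reproduce the 90%.** The Hussey and Hughes variance of the effect is

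Var = Iσ²(σ² + Tτ²) / [(IU − W)σ² + (U² + ITU − TW − IV)τ²],

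where U is the number of treated area-periods, W the sum of squared period totals and V the sum of squared area totals.

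- T = 12: U = 65, W = 485, V = 505, so IU − W = 165 and the τ² coefficient is 1155.
- T = 11: U = 55, W = V = 385, so IU − W = 165 and the τ² coefficient is 990.

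Worked example, 4.35% and T = 12 (τ² = 81.08): the numerator is 10 × 295.84 × (295.84 + 12 × 81.08) ≈ 3,753,600 and the denominator 165 × 295.84 + 1155 × 81.08 ≈ 142,460. Var ≈ 26.35 and SE = 5.13. Power = Φ(20.7/5.13 − 1.96) = 98.1%. The difference detectable with 90% power is (1.96 + 1.2816) × 5.13 = 16.6, or 8.0% of 207.

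| Reading of 4.35 | T | SE | Power | Detectable at 90% power |
|---|---|---|---|---|
| ratio, τ = 900 | 11 | 5.73 | 95.1% | 9.0% |
| ratio, τ = 900 | 12 | 5.54 | 96.2% | 8.7% |
| 0.435, τ = 90 | 11 | 5.73 | 95.1% | 9.0% |
| 0.435, τ = 90 | 12 | 5.54 | 96.2% | 8.7% |
| 4.35%, τ = 9.0 | 11 | 5.22 | 97.8% | 8.2% |
| 4.35%, τ = 9.0 | 12 | 5.13 | 98.1% | 8.0% |
| SD of 4.35 | 11 | 4.70 | 99.3% | 7.4% |
| SD of 4.35 | 12 | 4.68 | 99.3% | 7.3% |

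Exactly 90% power for 20.7 needs SE = 20.7/3.2415 = 6.39. With T = 12 that requires a within-site SD of 19.8 (ratio) or 22.0 (4.35%). The article's own text has "a maximum temporal standard deviation per site of 17.2 (range within sites 5–17").

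**4. Varying what is not printed** (σ = 17.2, two-sided unless stated):

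- Ten one-area steps, ratio reading, t reference (noncentral t): T = 11 gives 88.4% (8 df) or 89.4% (9 df); T = 12 gives 90.3% or 91.2%.
- Five steps of two areas, T = 6: 73.9% (ratio), 83.4% (4.35%), 89.3% (SD of 4.35). One-sided with 4.35%: 90.1%.
- Five consecutive steps of two areas, T = 12: 85.7% (ratio), 87.7% (4.35%), 90.1% (SD of 4.35).

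**The case against.** The strongest defence has four parts.

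- **A missing percent sign explains the number.** This is plausible: an SD of 9.0 is feasible. It is still a guess, and the text needs correcting either way.
- **The 90% can be recovered.** A reader might infer that no reading of the inputs returns it. The documents do not support that: a small-sample t reference or two areas per step come within 2 points of 90% for some readings. Which choice was made cannot be told from the article.
- **The gap is harmless.** A reader might infer that the trial is underpowered on its own figures. The documents do not support that either. In the one-area-per-step layout the inputs give more power than claimed, and the largest within-site SD was used. At σ = 17.2, whether 4.35 is a ratio, 0.435 or a percentage moves power by only 2 to 3 points, because the estimate rests mainly on within-area change. This stands and limits the importance of the point. Some two-area layouts do fall below 90%, but the article describes no such layout.
- **Step structure is detail that a condensed article may leave to the full protocol.** Also fair: its absence alone would be no finding. It matters here only because a printed input is wrong and the printed result cannot be recovered without it.

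Two further arguments should not be used. The reading of 4.35 would matter more at larger within-site SDs, but the article prints none. The mortality range under Setting ("ranging from 46.7 in Trafford to 71.9 per 100,000 in Manchester") concerns a different outcome and puts no bound on the spread of admission rates.

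**Conclusion.** The point holds in limited form. The 4.35 is wrong as written: as a unitless coefficient of variation it exceeds the maximum of 3.16 for ten non-negative rates, and this needs no assumption about the design. That the stated power does not follow is conditional on ten one-area monthly steps, 11 or 12 periods, σ = 17.2 per area-period and a two-sided z test. Under those assumptions power is about 95 to 96% (ratio or 0.435) or 98% (4.35%) against the stated 90%, and the detectable difference is about 8 to 9% against 10%. In that layout the discrepancy is 5 to 8 points on the conservative side. It is a defect of correctness and reproducibility in the power statement, not evidence of a shortfall in power. Whether local-authority variability suits intervention areas of one to three LSOAs is a separate question, not judged here.

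**What to change.** Replace the 4.35 with the between-site SD in rate units, or with a coefficient of variation carrying its unit, taken from the same Local Alcohol Profiles for England extract. State the number and length of periods, the areas crossing per step, the within-site SD entered, and the test used (sidedness and reference distribution). Rerun the Hussey and Hughes formula and print the power and detectable difference that these inputs give in place of the current 90% for 10%.

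The cost is one recalculation from data already extracted and a correction of a sentence or two. The number of areas need not change. The only downside is that the printed figure changes.

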**Fig. 1 Fig1:**
[figure not shown]
CICA Evaluation Logic Model

Additionally, we also considered the possible unintended consequences of the intervention (see Fig. 2). Few public health interventions and evaluations explicitly look at unintended harms and, although logic models considering positive consequences and outcomes are common, the consideration of the potential negative outcomes (and their mechanisms of action), or a ‘dark’ logic model, are less common [30]. According to Bonell et al. [31], not only is it important to produce a dark logic model ahead of the evaluation/intervention, or during it, but also the framework could be useful to evaluate the project retrospectively to see how it might have been strengthened. To develop the dark logic model we first created a matrix to hypothesise *a priori* the potential unintended consequences of CICA using a simple framework, adapted from Lorenc and Oliver’s five categories of harm (see Table 1) [30]. Each potential harm was reflected upon using one of three approaches recommended by Bonell et al. [31]: how agencies and structures may interact in unintended ways; comparative understanding across similar interventions; and consultation with individuals/groups with insights into local contexts and how interventions might operate within them. Evidence that supports or refutes the hypothesised unintended consequences of the intervention will benefit future design and minimise the risk of future harm [31].

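### The 84% power for the external comparison is claimed for the intervention LSOA but rests on a local-authority SD, a single-measurement formula and a one-sided test; at intervention-area level it is far lower

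*Protocol article*

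**What the plan says.** All references are to the Protocol article, section Statistical analysis and power calculation, unless another section is named.

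- **Level of the inputs.** "Statistical power analyses were conducted at local authority level rather than at the level of the intervention area". The reason given is that the exact areas were not yet fixed; the aggregated figures are offered as indicative for the stepped-wedge design.
- **Mean.** "The mean standardised alcohol-related hospital admission rate in these local authorities for the year 2014 was 207 (per 100,000 people").
- **SD.** The only measure of spread on the scale of admissions per 100,000 is this one: "maximum temporal standard deviation per site of 17.2 (range within sites 5–17").
- **Number of areas.** "With 10 areas and 12 month follow-up", stated for the stepped-wedge calculation. No number of control areas is stated.
- **External comparison.** "Assuming a standard comparison of independent means, 1-sided test, and significance level of 5" per cent. Changes in the admission rate of the intervention LSOA against the chosen comparison area "yield an 84% statistical power to detect a similar 10% decrease". For this comparison the text also says that "no additional clustering occurs".
- **Planned analysis.** Outcome evaluation places the analysis at the small intervention area and names hierarchical growth models and synthetic control series. The power section adds mixed-effects log-rate models for trends in matched areas.
- **Size of the areas.** Setting gives 1,648 people for the smallest intervention area and 5,586 for the largest.

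**The concern.** The power sentence names one unit (the intervention LSOA) and one quantity (a change relative to a comparison area). The only SD available to support it belongs to another unit (a whole local authority) and another quantity (a single measurement in one site over time). A local authority's rate rests on many more events than that of an area of one to three LSOAs, so its SD cannot be carried down.

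Two further choices need stating. The one-sided 5% test raises the figure and is not justified, while the stepped-wedge calculation quotes 5% without naming sides, so the 90% and the 84% may rest on different standards. The independent-means formula and the remark on clustering also do not describe matched areas measured repeatedly; the same section invokes repeated measures as the reason for a mixed model in the internal analysis.

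The stake is interpretation. A reader who trusts 84% power could take a null external result as evidence against a 10% reduction when the comparison had little chance of showing one.

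**Working it through.** **Inputs.** Mean 207 per 100,000, so a 10% decrease is 20.7. SD 17.2. Ten intervention areas. Ten control areas is an assumption, made because it reproduces the stated figure.

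**1. Reproduce the 84%.** Standard error = 17.2 × √(2/10) = 7.69. Standardised difference = 20.7 / 7.69 = 2.69.

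- One-sided 5%, normal: Φ(2.69 − 1.645) = 85.2%. Noncentral t, 18 df: 82.7%. These bracket 84%.
- Two-sided 5%, normal: Φ(2.69 − 1.960) = 76.8%. Noncentral t: 72.1%. Neither reproduces 84%.

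**2. A change in place of one measurement, still at local-authority level.** With one value before and one after, the SD of a change is 17.2 × √(2(1 − ρ)). With m independent values on each side it is 17.2 × √(2/m). The document gives neither ρ nor m.

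| Assumption | SD | Two-sided power (t) |
|---|---|---|
| one pre, one post, ρ = 0 | 24.3 | 44% (48% normal) |
| one pre, one post, ρ = 0.25 | 21.1 | 55% |
| ρ = 0.5, or m = 2 | 17.2 | 72% |
| m = 3 | 14.0 | 88% |
| ρ = 0.75, or m = 4 | 12.2 | 95% |

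Replacing the maximum SD by 11, the middle of the stated 5 to 17, gives 98% for a single measurement and 80% for the uncorrelated change (two-sided, t). At this level the true figure could be above or below 84%.

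**3. Intervention-area level.** Assume Poisson variation only, one year's rate, 10 v 10 areas, and all areas of the smallest or all of the largest size.

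- Expected admissions e: 1,648 × 207/100,000 = 3.4; 5,586 × 207/100,000 = 11.6.
- SD of the rate = √e / population × 100,000: 112 and 61 per 100,000, against the 17.2 used.
- Standardised difference = 20.7 / (SD × √0.2), which simplifies to 0.1 × √(5e): 0.41 and 0.76.
- Power (t): 11% and 18% one-sided; 7% and 11% two-sided.

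**4. How far more favourable assumptions help.** Only e matters in this formula, so tripling the rate and pooling three years at 207 have the same effect.

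- Three times the expected count (10.2 and 34.7): standardised differences 0.72 and 1.32, one-sided power 17% and 35%.
- Error-free counterfactual, all ten areas of the largest size, one year: pooled count 115.6, 10% is 11.56, SD √115.6 = 10.75, ratio 1.08. Power is 28% one-sided and 19% two-sided (normal).
- The same at three times the rate: pooled count 346.9, ratio 34.69/18.62 = 1.86. Power is 59% one-sided and 46% two-sided.
- For 84% one-sided in a 10 v 10 comparison (normal), 0.1 × √(5e) must equal 1.645 + 0.994 = 2.64, so e is about 139 admissions per area, against 3.4 to 11.6 a year.

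**The case against.** **The figure is not an arithmetic error, and its assumptions are disclosed.** This stands. The 84% follows from the stated inputs, the one-sided test is written down, and the use of local-authority data is admitted with a reason. But the admission concerns indications for the stepped-wedge design, while the external sentence attaches 84% to the intervention LSOA. Disclosing the source of the SD does not make the result true at a level with a handful of events a year.

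**A reader might infer that power for the change is 44% to 72%.** The document does not support that range. The 44% needs one uncorrelated pre-post pair at the largest site SD, and the 72% is the two-sided single-measurement figure. The plan compares repeated trends with mixed or hierarchical models and Bayesian time series, whose power cannot be derived from what is stated.

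**A reader might infer that the external evaluation could not report an adverse result**, and set this against the statement that "we also considered the possible unintended consequences of the intervention". That does not follow. The one-sided test appears only as a power assumption; no sidedness is fixed for the analyses, and the effect is read from the measured and counterfactual trends without restriction on direction. The harms listed in Table 1 do not include a rise in area admission rates.

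**The planned models already handle repeated measures, and ignoring positive correlation between matched areas is usually conservative.** Largely accepted. What remains is that the clustering remark is wrong as a description of the data and conflicts with those models.

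**The Poisson figures use the authority-average rate, although areas were chosen for high harm.** Accepted. Higher rates or longer follow-up raise power, but tripling the expected count leaves it well short of 84%.

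**Conclusion.** The 84% is wrong as stated, because it is claimed for a unit to which its SD does not apply. On the document's own inputs it needs the one-sided test; two-sided it is about 72% (t) to 77% (normal). At intervention-area level, power for one year's rate is about 11% to 18% one-sided and 7% to 11% two-sided, and about 17% to 35% one-sided at three times the rate.

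These figures assume a 10 v 10 layout, Poisson variation only and a simple comparison of one rate per area. Overdispersion would lower them; more events, more time points or a well-predicting control series would raise them. Power for the planned trend models is unknown from the document.

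This should be corrected, but it does not undermine the trial. It concerns the second of two evaluations, uses routine data and changes no sample size.

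**What to change.** - Withdraw the 84% as a statement about the intervention LSOA. If it is kept, label it a local-authority-level, one-sided, single-measurement illustration, with the number of areas per group.
- Recompute power at intervention-area level with an area-level SD (or event counts with an allowance for overdispersion) and a two-sided 5% test. Base it on the planned mixed-effects trend model, stating the number of control areas, the time points before and after, and the within-area correlation. Where an input is unknown, show a range.
- State the sidedness of the stepped-wedge calculation, so that the two power figures can be compared.
- Replace the remark on clustering with a statement that repeated measurements within areas, and matched sets, are accounted for in the model.

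The cost is a recalculation, some rewording and a less favourable published figure. No new data collection is needed and the design does not change.

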### Economic evaluation

The economic evaluation aims to conduct a cost consequences analysis of the CICA programme. It will do this through:Identifying set-up and running costs using a standardised costing exercise (examination of commissioning documents and contracts);Resolving costs by sector (health, ambulance and police) before, during and after the CICA set up;Quantifying benefits due to reduced hospital admissions, ambulance call outs, emergency department use, crime and anti-social behaviour.

The costs of training, delivery and support elements of the intervention will be estimated. The economic evaluation will build on the outcome evaluation by attributing costs to the health performance indicators collected on primary outcomes. UK Treasury approved methods published by New Economy will underpin the cost-consequences analysis (CCA) and unit costs are based on the New Economy Unit Cost Database [41].

A standard costing exercise will use documents and contracts to identify resources and costs required to deliver the CICA intervention in each local authority. Standardised methods allow comparability of costs. The economic evaluation follows a cost-consequences analysis which is an approach that is favoured when costs and outcomes fall on a range of budget-holders and government agencies enabling cost and consequence domains to be presented in a disaggregated form [42, 43]. This will enable decision makers to assess results using different relevant perspectives.

The key cost categories identified include the set up cost for the intervention area, comprising staff costs, consumables and overheads (premises). In terms of consequences, this comprises an analysis of health benefits, changes in health care resource utilisation as a consequence of alcohol use (A&E attendances, hospital inpatient stays, ambulance service costs), and changes in contacts with the criminal justice system.

The outcome analysis uses mixed-effects log-rate models and differences-in-differences models to evaluate changes relative to propensity-score-matched controls and will use Bayesian structural time series to model the synthetic control areas; both to assess and compare potential changes in the health care and criminal justice resources before and after CICA interventions. The economic component of the study will follow the same statistical methods used in the outcome analysis and applies unit costs to the resource indicators to derive costs for each domain. These costs will be presented in a CCA framework, disaggregated in terms of costs to individual stakeholders and different cost domains.

